- Evaluation of resolution of the infection and potential recurrence of infection according to the judgment of the attending physician
- Evaluation of potential adverse events

Visit 10 is on day 10. Procedures of this day include:

- Recording of SOFA score (see APPENDIX II); available blood cell count, biochemistry, coagulation times, urine output, blood gases, available radiological findings, clinically relevant microbiology and antimicrobial susceptibility testing, administered antimicrobials, other administered drugs and need for source infection control either by percutaneous interventions or by any operation.
- Survival status
- Evaluation of resolution of the infection and potential recurrence of infection according to the attending physician
- Sampling of 33 ml of venous blood; 9ml is collected into one pyrogen-free tube; and 24ml is collected into EDTA-coated tubes
- Evaluation of potential adverse events

Visits 11-28 are on days 11-28 respectively. They include

- Recording of SOFA score if available
- Administered antimicrobials, other administered drugs and need for source infection control either by percutaneous interventions or by any operation.
- Survival status
- Evaluation of resolution of the infection and potential infection recurrence according to the judgment of the attending physician
- Evaluation of potential adverse events

If the patient is discharged before day 28, a phone call will be performed on day 28 to assess survival status, need for new hospitalization or antibiotic therapy and potential adverse events. End-of-life decisions, if any, will be recorded.

Last visit: A phone call follow-up will be done on day 90 to assess survival status. If available, data concerning any new hospitalization, or antibiotic cure and potential adverse events will be collected during that phone call. Moreover, a self or proxy-assessment of health-related quality of life will be performed through the EQ-5D-3L^™^ questionnaire on the same visit (see APPENDIX IV) ^18^.

All information will be recorded on a specific paper Case Report Form (CRF).

The procedure to follow at each study visit is shown in APPENDIX V.

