**POWER CALCULATION**

This is done for the primary study endpoint. We are planning a study of independent cases and controls with 1 control per case. Prior data indicate that the mortality among placebo-treated patients with sepsis and respiratory dysfunction was 55% and that this was decreased to 30%^11^. We need to study 55 subjects into each group to be able to reject the null hypothesis that the failure rates for both groups are equal with probability (power) 0.8. The Type I error probability associated with this test of this null hypothesis is 0.10. We will use a continuity-corrected chi-squared statistic or Fisher’s exact test to evaluate this null hypothesis.

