**ADVERSE EVENTS**

Adverse events (AEs) and Serious Adverse Events (SAEs) will be collected from baseline until the last patient’s last evaluation. An adverse event is any undesirable medical occurrence in a subject receiving a pharmaceutical product and which does not necessarily have a causal link with this treatment. The adverse event may be a sign, a symptom, or an abnormal laboratory finding.

An adverse reaction is any undesirable and unintended reaction due to investigational medicine product administration (or intervention), related with any dose administrated. If an adverse event/ reaction meets any of the following criteria, it is considered as a *Serious Adverse Event/ Reaction* (SAE):

- Death
- Life-threatening situation The subject was at risk of death at the time of the adverse event/ experience. It does not refer to the hypothetical risk of death if the AE/ adverse reaction were more severe or were to progress.
- Hospitalization or prolongation of existing hospitalization
- Persistent or significant disability/ incapacity Any AE having an outcome that is associated with a substantial disruption of the ability to carry out normal life functions, including the ability to work. This is not intended to include transient interruption of daily activities.
- Congenital anomaly/ birth defects Any structural abnormality in subject’s offspring that occurs after intrauterine exposure to treatment.
- Important medical events/ experiences that may not result in death, be life-threatening, or require hospitalization, may be considered as SAE when, based upon appropriate medical judgment, they may jeopardize the subject and may require medical or surgical intervention to prevent one of the outcomes listed above, i.e. death, a life-threatening adverse event/experience, inpatient hospitalization or prolongation of existing hospitalization, a persistent or significant disability/ incapacity, or a congenital abnormality/ birth defect. Examples of such medical events/ experiences include allergic bronchospasm requiring intensive treatment in an emergency room or at home, blood dyscrasias or convulsions that do not result in inpatient hospitalization, or the development of drug dependency or drug abuse.
- Spontaneous and elective abortions experienced by study subject

*A non-serious adverse event* is one that does not meet the previous definition of a SAE. The severity of the non-serious adverse events will be graded using the following definitions:

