**Anxiety/Depression**

I am not anxious or depressed ❑

I am moderately anxious or depressed ❑

I am extremely anxious or depressed ❑

To help people say how good or bad a health state is, we have drawn a scale (rather like a thermometer) on which the best state you can imagine is marked **100** and the worst state you can imagine is marked **0**.

We would like you to indicate on this scale how good or bad your own health is today, in your opinion. Please do this by drawing a line from the box below to whichever point on the scale indicates how good or bad your health state is today.

Best imaginable health state

9 0

8 0

7 0

6 0

5 0

4 0

3 0

2 0

1 0

100

0

Your own health state today

Worst imaginable

health state

**APPENDIX V** Procedures on each study visit (until day 28 or until hospital discharge)

|  | **Study visits** | | | | | | | | | | | | | | | | | | | | | | | | | | | | |  |
| --- | --- | --- | --- | --- | --- | --- | --- | --- | --- | --- | --- | --- | --- | --- | --- | --- | --- | --- | --- | --- | --- | --- | --- | --- | --- | --- | --- | --- | --- | --- |
|  | **1** | **2** | **3** | **4** | **5** | **6** | **7** | **8** | **9** | **10** | **11** | **12** | **13** | **14** | **15** | **16** | **17** | **18** | **19** | **20** | **21** | **22** | **23** | **24** | **25** | **26** | **27** | **28** | **Last** | |
| Study drug | x | x | x | x |  |  |  |  |  |  |  |  |  |  |  |  |  |  |  |  |  |  |  |  |  |  |  |  |  | |
| SOFA score* | x | x | x | x | x | x | x | x | x | x | x | x | x | x | x | x | x | x | x | x | x | x | x | x | x | x | x | x |  | |
| Survival |  | x | x | x | x | x | x | x | x | x | x | x | x | x | x | x | x | x | x | x | x | x | x | x | x | x | x | x | x | |
| CCI | x |  |  |  |  |  |  |  |  |  |  |  |  |  |  |  |  |  |  |  |  |  |  |  |  |  |  |  |  | |
| APACHE score | x |  |  |  |  |  |  |  |  |  |  |  |  |  |  |  |  |  |  |  |  |  |  |  |  |  |  |  |  | |
| Vital signs** | x | x | x | x | x | x | x | x | x | x | x | x | x | x | x | x | x | x | x | x | x | x | x | x | x | x | x | x |  | |
| Concomitant drugs/ procedures | x | x | x | x | x | x | x | x | x | x | x | x | x | x | x | x | x | x | x | x | x | x | x | x | x | x | x | x |  | |
| Infectious site identification | x |  |  | x |  |  |  |  |  |  |  |  |  |  |  |  |  |  |  |  |  |  |  |  |  |  |  |  |  | |

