| Resolution/ recurrence of infection** |  |  |  |  |  |  | x | x | x | x | x | x | x | x | x | x | x | x | x | x | x | x | x | x | x | x | x | x |  | |
| AE monitoring | x | x | x | x | x | x | x | x | x | x |  |  |  |  |  |  |  |  |  |  |  |  |  |  |  |  |  |  |  | |
| Microbiology** | x | x | x | x | x | x | x | x | x | x | x | x | x | x | x | x | x | x | x | x | x | x | x | x | x | x | x | x |  | |
| Pregnancy test*** | x |  |  |  |  |  |  |  |  |  |  |  |  |  |  |  |  |  |  |  |  |  |  |  |  |  |  |  |  | |
| PAX Gene | x |  |  |  | x |  |  |  |  |  |  |  |  |  |  |  |  |  |  |  |  |  |  |  |  |  |  |  |  | |
| Serum metabolomics | x |  |  |  | x |  |  |  |  | x |  |  |  |  |  |  |  |  |  |  |  |  |  |  |  |  |  |  |  | |
| PBMCs isolation | x |  |  |  | x |  |  |  |  | x |  |  |  |  |  |  |  |  |  |  |  |  |  |  |  |  |  |  |  | |
| Stool sample | x |  |  |  | x |  |  |  |  |  |  |  |  |  |  |  |  |  |  |  |  |  |  |  |  |  |  |  |  | |

- * SOFA score: if available according to usual clinical practice. On days where SOFA components are not available (e.g. no blood analysis programed by the physician or discharged patient), the last known value will be recorded.
- ** If available and justified by clinical context ***For female patients of reproductive age

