
# 4. Statistical Analysis Plan

The INtravenous CLArithromycin in Sepsis with multiple organ dysfunction Syndrome (INCLASS) study aims to assess the efficacy of clarithromycin as adjunctive treatment in reducing all-cause 28-day mortality among severely ill patients with sepsis. The study also aims to provide insight on the mechanism of action underlying clinical outcomes. The study statistical analysis plan (SAP) was conducted by the protocol authors ([name] and [name]), as well as the study statistician [name]. [name] provided statistical advice on bioinformatics for RNA sequencing. The SAP was established on 26/06/2019, at the end of enrollment and before the unmasking, the database lock and the end of the follow-up period.

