**Safety outcomes**

- Adverse events (AEs)
- Serious adverse events (SAEs)
- Suspected unexpected serious adverse reactions (SUSARs)

Patients are followed-up daily until day 28 or hospital discharge (whatever comes first). In case of earlier discharge, the primary outcome, is assessed by phone call at day 28. 90-day mortality and quality of life by the EuroQol**^®^** 5-dimension 3-level (EQ-5D-3L) questionnaire (1), in case of discharge, are also assessed by phone call with the patient or their caregiver. Safety outomes are captured daily until day 28 or discharge (whichever comes first) and as patient or provider-reported events until day 90. All other secondary outcomes are assessed until day 28 or discharge.

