**Safety outcomes**

The percentage of patients having at least one category of AE, SAE and SUSAR, will be compared by the Fisher’s exact test.

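### The Appendix V schedule ends adverse-event monitoring at visit 10, while the protocol text and the SAP continue it to day 28 and day 90; the row should be corrected and the SAP comparison tied to a stated window

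*Supplement*

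**What the plan says.** Four places in the current documents set the period of AE capture.

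- **Protocol version 2, Appendix V.** The table is titled "Procedures on each study visit (until day 28 or until hospital discharge" and has columns for visits 1 to 28 and a last visit. Its AE row reads "AE monitoring | x | x | x | x | x | x | x | x | x | x", and the remaining cells are blank.
- **Protocol version 2, Study visits.** AE evaluation is listed under visits 11-28. For patients already discharged, "a phone call will be performed on day 28 to assess survival status, need for new hospitalization or antibiotic therapy and potential adverse events". AEs are also collected at the day-90 call where the information is available. The section closes by naming Appendix V as the procedure for each visit.
- **Protocol version 2, Adverse events.** "Adverse events (AEs) and Serious Adverse Events (SAEs) will be collected from baseline until the last patient’s last evaluation".
- **SAP, Safety outcomes (outcome list).** "Safety outomes are captured daily until day 28 or discharge (whichever comes first) and as patient or provider-reported events until day 90".

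The second SAP section headed Safety outcomes gives the analysis: "The percentage of patients having at least one category of AE, SAE and SUSAR, will be compared by the Fisher’s exact test". It states no window.

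**The concern.** The schedule table contradicts three other passages, and it is an operative instruction because the visit text refers sites to it. A site that filled in CRFs from the table would stop evaluating AEs after visit 10, and events on days 11-28 could be lost.

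The analysis sentence then pools whatever was captured into one percentage per arm. The SAP describes two modes of capture, active daily evaluation to day 28 or discharge and reported events to day 90, but does not say whether the second counts towards the tested percentage. The share of patients with at least one event rises with time observed, so a reader needs to know the window and how long each arm was under observation.

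**Working it through.** **1. Where each passage ends AE capture**

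| Source | End of AE capture |
|---|---|
| Protocol v2, Appendix V | Visit 10 |
| Protocol v2, Study visits | Day 28 (visit, or call if discharged); day 90 if available |
| Protocol v2, Adverse events | Last evaluation; the last scheduled contact is the day-90 call |
| SAP, Safety outcomes (list) | Day 28 or discharge (daily); day 90 (reported) |
| SAP, Safety outcomes (analysis) | Not stated |

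Three passages agree and Appendix V is the outlier. A text-extraction fault is unlikely: the SOFA, survival and microbiology rows of the same table run to visit 28, and the version 1 schedule carries the same ten AE marks. The gap is 28 − 10 = 18 daily evaluations, or 18/28 = 64% of them.

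**2. How much observation lies in days 11-28**

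The Power calculation gives the mortality inputs: "Prior data indicate that the mortality among placebo-treated patients with sepsis and respiratory dysfunction was 55% and that this was decreased to 30" per cent, with 55 patients per arm. Assume a constant death hazard and no discharge before day 28.

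- Placebo hazard: −ln(0.45)/28 = 0.02852 per day. Clarithromycin: −ln(0.70)/28 = 0.01274 per day.
- Mean days alive to time t = (1 − exp(−λt))/λ.
- To day 10: 8.70 vs 9.39. To day 28: 19.29 vs 23.55. Days 11-28: 10.59 vs 14.16.
- Times 55: 582 vs 779 patient-days in days 11-28, which is 55% and 60% of each arm's 28-day total.

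**3. How many patients with an AE would be missed**

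The documents give no AE rate, so assume a hazard a of 1%, 2% or 3% per day, equal in both arms. P(first AE before death, by t) = a/(a+λ) × (1 − exp(−(a+λ)t)).

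| a per day | Days 1-10, placebo / clarithromycin | Days 1-28, placebo / clarithromycin | Share of the 28-day count missed if capture stops at day 10 |
|---|---|---|---|
| 1% | 8.3% / 8.9% | 17.1% / 20.7% | 52% / 57% |
| 2% | 15.8% / 17.1% | 30.6% / 36.7% | 48% / 53% |
| 3% | 22.7% / 24.4% | 41.3% / 49.0% | 45% / 50% |

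The last column is (28-day − 10-day)/28-day. It is an upper limit, reached only if every site stopped at visit 10.

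**4. What differential survival adds**

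With no drug effect on AEs, the day 1-28 columns still differ by 3.6 to 7.7 points against clarithromycin, and the day 1-10 columns by 0.6 to 1.7. The cause is longer survival, not the schedule conflict. Sensitivity of the day-28 gap over the same AE range:

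- Deaths weighted early (Weibull, shape 0.6, same 28-day mortality): 4.4 to 9.7 points.
- Capture ending at discharge, with discharge from day 7 at 2% per day on placebo and 4% on clarithromycin: 1.1 to 2.6 points.
- The same with 6% per day on clarithromycin: −0.4 to −0.5 points.

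At 2% per day and without discharge, the chance that a two-sided Fisher test at 0.05 is significant against clarithromycin is 2% on days 1-10 and 7% on days 1-28. With discharge at 2% vs 4% per day, the day-28 figure is 2.6%.

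**The case against.** **The SAP already supplies a window.** The two sections headed Safety outcomes cover the same three items, and the first gives their capture period. The General principles add that the primary manuscript covers clinical data to day 90. This largely stands. A reader might infer from Appendix V that the Fisher comparison could mean days 1-10, but no SAP passage sets a day-10 cut-off. What stays open is day 28 against day 90, and that is mainly missing detail.

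**Appendix V is a clerical slip that probably did no harm.** The table is loose elsewhere: its resolution/recurrence row starts at visit 7, although the visit text starts at visit 5. Investigators must report every AE, and monitors verify CRFs against source documents. It is also fair that dosing ends on day 4. The protocol's causality window runs five half-lives beyond that, so it would reach day 10 only for a half-life of (10 − 4)/5 = 1.2 days or more; the documents give no half-life. Nothing shows that any site stopped at visit 10. But the visit text sends sites to this table, and the planned percentages count all AEs, not only those judged related.

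**The gap between arms is not caused by the conflict.** This stands. A reader might take the 3.6 to 7.7 points as bias from inconsistent windows. They come from differential survival, would arise on any crude AE percentage if mortality differs, and are larger on the day-28 window recommended here. Size and even direction depend on assumed discharge rates. They justify showing patient-days and nothing stronger.

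**Conclusion.** The Appendix V row is wrong as written and conflicts with three current passages. Followed literally, it removes 18 of 28 daily AE evaluations and, on the assumptions shown, about half of the patients with an AE by day 28. How far this happened cannot be told from the documents.

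Randomisation is stratified by site (SAP, Randomization), so any mixture of practices should be similar in the two arms. The main effect is an undercount of late events. The documents do not support a claim that the comparison between arms is biased by the schedule, or that the Fisher result would often change. Mortality analyses are untouched, so the primary conclusion is unaffected.

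The SAP sentence needs a smaller repair: it should say whether the percentages stop at day 28 or include reported events to day 90. The size estimates rest on the plan's 55% and 30% mortality, a constant death hazard, no early discharge, and an assumed AE hazard of 1-3% per day. The contradiction itself rests on none of these.

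**What to change.** 1. **Appendix V:** extend the AE row to visits 11-28 and the last visit.
2. **SAP, Safety outcomes (analysis):** state that the percentages count AEs, SAEs and SUSARs from baseline to day 28 in all randomised patients, including events found at the day-28 call, and that reported events from day 29 to day 90 are shown separately by arm. Starting at baseline agrees with the Adverse events section and covers randomised patients who were never dosed. Not stopping at discharge keeps the events that the day-28 call is meant to find.
3. **Beside the percentages:** give patient-days of observation per arm, because under the plan's own mortality assumption the arms are observed for different lengths of time.
4. **Before unmasking:** check the CRFs by site, blinded to arm, for AE entries after visit 10, and report any gap. The SAP is dated "at the end of enrollment and before the unmasking, the database lock and the end of the follow-up period", so this was feasible. The main window should not change in response to what the check shows.

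Cost: one table row, one or two SAP sentences and a CRF check. No visit or test is added. AE onset must be dated in the CRF; survival is already recorded. The downside is that correcting the table at the end of enrollment cannot recover late events that were never recorded.

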**Missing values**

Missing values will be treated as such, and the number and percentage of patients or events entering each step of the analysis will be provided. The Little’s test will be used to assess whether missing values are missing completely at random.

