**Sample size calculation**

This is done for the primary endpoint. Based on previous studies, we anticipated a 25% reduction of mortality among patients with sepsis and respiratory dysfunction, treated with clarithromycin. To detect this difference with a type-I error of 0.10 and a type-II error of 0.8 and anticipating a 10% loss to follow-up, 55 patients need to be enrolled in each study arm.

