**Populations**

Analyses will be performed on an intention-to-treat (ITT) basis, including all randomized patients, independently of wheather they received the sudy intervention. The ITT population will enter analysis of the primary and all secondary outcomes. In case of consent withdrawal, all data collected prior to this point will be excluded.

The following subgroups of patients are potentially identified:

- Enrolled inside and outside of the intensive care unit (ICU)
- Enrollement in Greece and in Belgium
- Presence or absence of septic shock
- Presence or absence of acute respiratory dysfunction syndrome (ARDS)
- Extremely high severity, defined as patients within the highest quartile of SOFA score, vs all others.
- Presenting pneumonia, intra-abdominal infection or primary Gram-negative bacteremia
- Presence or absence of a Gram-negative pathogen (among infections with identified pathogen only)
- Adequate vs non-adequate empirical antimicrobial treatment (among infections with identified pathogen only). Empirical antimicrobial treatment (defined as the regimen given within 48 hours from infection onset, when cultures are pending) is considered as adequate when administered at the indicated dose and with penetration to the infected site; provided that the identified pathogen has documented or reasonably suspected susceptibility (e.g. metronidazole for *Clostridioides difficile* infection)
- Per protocol (PP) population, defined by patients receiving the entire intervention (all 4 daily doses)

Subgroup analyses will be performed for mortality outcomes (28-day and 90-day).

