**General principles**

- This analysis plan and the primary manuscript will include clinical data up to 90 days, transcriptomic and cell population (by flow cytometry) analyses; the entire cost-effectiveness analysis, cytokine analysis (including serum cytokine concentrations and cytokine production from supernatants of ex-vivo stimulated peripheral blood mononuclear cells-PBMCs) and microbiome analysis will be reported separately.
- Regarding flow cytometry analysis (including cell population and HLA-DR analysis), only samples from patients enrolled in sites proximal to the central lab (Athens) could be included in the current study.
- Regarding trasncriptomic analysis, only a subset of sample sequencing could be covered by the study funding at the time of the present statistical analysis plan. Thus, it was decided to only include in the primary manuscript samples from the subgroup of patients of extremely high severity (within the highest quartile of baseline SOFA score), to demonstrate differences between death and survival. The entire transcriptomic analysis, combined with metabolome, cytokine and microbiome analysis will be reported separately.
- All p-values will be two-sided and the level of significance will be <0.05.
- No interim analysis is planned.
- Regarding clinical data, cell populations and HLA-DR measurements, no adjustment for multiple comparisons is planned and all secondary outcomes will be viewed as exploratory. For transcriptomic data, statistically significant differences will be defined by Benjamini & Hochberg adjusted probabilities < 0.05 and absolute fold expression ≤−1.5 or ≥1.5.
- Analyses will be conducted primarily by the SPSS statistical software, version 24 (IBM) or later; transcriptomic data twill be analysed in the R statistical framework (Version 3.51, R Core Team 2014. R: A language and environment for statistical computing. R Foundation for Statistical Computing, Vienna, Austria)
- Results will be presented by order of importance, starting with the primary outcome first. Due to the nature of the study, additional exploratory analyses will be performed based on the primary and secondary outcomes, in an effort to identify potential host immune pathways modulated by the study drug.

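### The missing-data rule in effect drops patients with unknown day-28 status from the primary test, which conflicts with the stated ITT population and probably overstates mortality in each arm

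*Supplement*

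**What the plan says.** - **Expected loss.** The SAP, Sample size calculation, arrives at 55 patients per arm "anticipating a 10% loss to follow-up".
- **Analysis population.** The SAP, Populations, defines ITT as "including all randomized patients, independently of wheather they received the sudy intervention". It adds that when consent is withdrawn, everything collected up to then is excluded.
- **Primary test.** The SAP, Analyses for the primary outcome, plans Fisher's exact test on a 2x2 table, on an ITT basis, confirmed by logistic regression. It also plans a log-rank test, a Cox model and the absolute difference in mortality with its 95% CI.
- **How day-28 status is obtained.** Protocol version 2, Study visits, records survival at each daily visit in hospital. After discharge, the SAP (Safety outcomes) says: "In case of earlier discharge, the primary outcome, is assessed by phone call at day 28". Both documents also plan a day-90 call that assesses survival.
- **Missing data.** The SAP, Missing values, says "Missing values will be treated as such" and promises the number and percentage of patients entering each step. It then says: "The Little’s test will be used to assess whether missing values are missing completely at random". Nothing follows from the result of that test.

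Neither document gives an imputation rule, a censoring rule or a sensitivity analysis for unknown day-28 status. The protocol does carry forward the last known value for SOFA when components are unavailable, and names the discharged patient as an example (Appendix V). It has no such rule for mortality.

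**The concern.** The plan promises an analysis of everyone randomised and then sets a rule under which the primary test covers fewer. The patients who drop out of the table are not a random sample. A patient who dies in hospital is recorded as dead. A patient lost to follow-up has left hospital alive and could not be traced. Removing such patients takes mostly survivors out of the denominator and leaves the deaths in the numerator.

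Two quantities are at stake. The first is the mortality reported in each arm, which would come out too high. The second is the treatment comparison, which would be distorted if one arm loses more of its survivors than the other. Little's test does not protect against either: it can show that missingness is related to observed variables, but not to the unobserved vital status.

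**Working it through.** **Step 1. The plan's own figure.** Inputs from Protocol version 2, Power calculation: mortality 55% and 30%, power 0.80, one control per case, and "The Type I error probability associated with this test of this null hypothesis is 0.10". With a two-sided test and average mortality 0.425:

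n = [1.645·√(2·0.425·0.575) + 0.842·√(0.55·0.45 + 0.30·0.70)]² / 0.25² = 47.3, so 48 per arm.

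With continuity correction: (47.3/4)·[1 + √(1 + 4/(47.3·0.25))]² = 55.0, so 55 per arm with no room for loss. Without it, 48/0.90 = 53.3, so 54 per arm with 10% loss. The stated 55 is reproduced within two patients either way. Ten per cent of 110 is 11 patients.

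**Step 2. Level of mortality in each arm.** Let p be true mortality, L the share of the arm lost and s the share of the lost who are alive. Complete-case mortality is (p − L(1 − s))/(1 − L). The documents do not give s; 80% to 100% is an assumed range. With L = 0.10:

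| Alive among the lost | Placebo (true 55%) | Clarithromycin (true 30%) |
| --- | --- | --- |
| 100% | 0.55/0.90 = 61.1% | 0.30/0.90 = 33.3% |
| 90% | 0.54/0.90 = 60.0% | 0.29/0.90 = 32.2% |
| 80% | 0.53/0.90 = 58.9% | 0.28/0.90 = 31.1% |

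The overstatement is 3.9 to 6.1 points on placebo and 1.1 to 3.3 points on clarithromycin.

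**Step 3. Treatment comparison.** Suppose first that the same share q of survivors is lost in both arms, with 10% lost overall: q = 0.10/0.575 = 17.4%. Mortality becomes p/(p + (1 − p)(1 − q)), that is 59.7% and 34.2%. The difference is 25.5 points against a true 25, and the odds ratio stays at 0.351.

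Now let the share of the arm lost vary, with all the lost alive, so that mortality is p/(1 − L):

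| Lost, placebo / clarithromycin | Survivors lost (of 45% / 70%) | Mortality | Difference |
| --- | --- | --- | --- |
| 10% / 10% | 22.2% / 14.3% | 61.1% / 33.3% | 27.8 |
| 5% / 15% | 11.1% / 21.4% | 57.9% / 35.3% | 22.6 |
| 15% / 5% | 33.3% / 7.1% | 64.7% / 31.6% | 33.1 |

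The first row shows that equal loss per arm is not equal loss of survivors when mortality differs. With equal true mortality of 42.5%, a 5%/15% split gives 0.425/0.95 = 44.7% against 0.425/0.85 = 50.0%, a false difference of 5.3 points.

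**Step 4. In patients.** Take 30/55 against 17/55 deaths as an illustration and remove survivors only. Fisher's test is two-sided, as in the SAP, General principles: "All p-values will be two-sided and the level of significance will be <0.05".

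| Survivors lost, placebo / clarithromycin | Observed | Difference | p |
| --- | --- | --- | --- |
| 0 / 0 | 30/55 v 17/55 | 23.6 | 0.020 |
| 5 / 5 | 30/50 v 17/50 | 26.0 | 0.016 |
| 4 / 7 | 30/51 v 17/48 | 23.4 | 0.027 |
| 3 / 8 | 30/52 v 17/47 | 21.5 | 0.044 |
| 2 / 9 | 30/53 v 17/46 | 19.6 | 0.069 |

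**Step 5. Bounds.** With 28/50 against 15/50 observed and 5 lost per arm, the complete-case difference is 26.0 points (p = 0.015). Counting all the lost as alive gives 28/55 v 15/55, 23.6 points (p = 0.019). The extremes are 28/55 v 20/55, 14.5 points (p = 0.18), and 33/55 v 15/55, 32.7 points (p = 0.001).

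**The case against.** The strongest reply is that the rule may be harmless in practice and that the plan already holds part of the answer.

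- **The SAP never says complete case.** That is correct, and the log-rank and Cox analyses can keep lost patients as censored. But Fisher's test is the primary test and a 2x2 table has no place for an unknown outcome. The promise to report numbers entering each step makes exclusions visible without removing their effect. No censoring rule is given either.
- **A reader might infer that only discharged patients can be missing, so the missing are survivors by construction.** The documents do not support this. Withdrawal of consent removes all earlier data, can occur in hospital, and has no known direction.
- **The day-28 call is not the last chance.** A patient missed then but found alive on day 90 was alive on day 28. The 10% is a planning allowance; permanent loss of day-28 status may be smaller.
- **A reader might infer that the treatment effect is necessarily biased.** It is not. With equal loss of survivors the odds ratio is unchanged and the difference moves by half a point.
- **A reader might infer that the planned loss would overturn significance.** Among the survivor-loss examples only the 2 v 9 split crosses 0.05. It removes 8% of placebo survivors (2/25) and 24% of clarithromycin survivors (9/38), and no document supports such an imbalance in a double-blind trial. The outer bounds in Step 5 require all the lost in one arm to have died, which goes against the expectation that most are alive. They are a stress test, not a forecast.

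What remains is that the primary test has no stated rule for unknown status, conflicts with its own population definition, and has no sensitivity analysis behind it.

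**Conclusion.** The concern holds in a limited form. Followed as written, the SAP takes patients with unknown day-28 status out of its primary test while describing that test as covering all randomised patients. Under the planned 10% loss, and assuming that 80% to 100% of the lost are alive, mortality would be overstated by about 1 to 6 points, more on placebo than on clarithromycin. Bias in the odds ratio depends on unequal loss of survivors. That is possible, because the protocol's Introduction reports earlier weaning and faster resolution of pneumonia on clarithromycin in a previous trial, but the plan gives no discharge or loss rates by arm from which to size it. A change in the study's conclusion is possible but not shown to be likely. This should be corrected; it does not invalidate the design.

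**What to change.** 1. Keep every randomised patient in the primary analysis where consent allows, and report withdrawals by arm.
2. Use the day-90 call, including any date of death learned from it, to recover day-28 status.
3. State how a status that stays unknown enters Fisher's test and the logistic model, for example by counting a patient last known alive at discharge as alive.
4. Report Kaplan-Meier 28-day mortality by arm, and state that the planned log-rank and Cox analyses censor at the date last known alive.
5. Add a best/worst-case or tipping-point table for unknown status.
6. Little's test may stay, but its result should not be used to justify leaving patients out.

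The cost is a few sentences in the SAP and one table, from data already being collected. The SAP was set before unmasking and database lock, so these rules could be fixed blind. The price is a stated assumption: that patients alive at discharge are alive at day 28 or, for the censored analyses, that the lost carry the same risk as those still followed. The second may still lean towards overstating mortality, since patients who have gone home are probably at lower risk. The table in item 5 shows how much depends on either.
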